### Follow up

The follow up period consists of 4 weeks with face-to-face visits at Day 7, 14 and 28. At each of these visits women will be seen by a research midwife or doctor. Hb, ferritin and CRP will be checked and results recorded in the study file. Patients will have been discharged with completed pathology forms to facilitate compliance with follow-up laboratory testing. Women will also undergo a clinical examination following a specified checklist to assess for any features of infection or other adverse outcomes . Symptom scores using the three specified scales will be collected at each of the follow up sessions. Research midwives will make all effort to ensure compliance with follow up and can facilitate home visits, including pathology collections if required.

### Monitoring/reporting of data

Given the potential for serious adverse events with each treatment, an independent Data Safety and Monitoring Board has been appointed at the primary study site consisting of a consultant obstetrician, haematologist and anaesthetist who are not directly involved with the study design or execution, as well as an independent research midwife and a statistician. Members will be provided with a charter prior to commencement of the study by study researchers requiring them to convene every 2 months for the duration of the study where they will review the data for completeness, accuracy and to identify incidences and severity of any adverse reactions and their management.

If the total incidence of severe adverse reactions (i.e. anaphylaxis, hematological reaction) exceeds 2 per 50 participants at any time in either treatment group, or if the difference in incidence of serious adverse events is greater than 50%, the study will be suspended until further review. Unscheduled DSMB meetings will be called whenever severe adverse reactions occur in either treatment group.

Conclusions and recommendations regarding study modifications will be presented to the principal researchers after each DSMB meeting and attention to these recommendations will be reviewed at subsequent meetings. Final decisions to terminate the study will be made by study researchers in consultation with the DMSB and the ethics committee.

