## Background

Post-partum haemorrhage (PPH) commonly complicates pregnancy and can result in acute anaemia [1]. Up to 10% of women with blood loss in excess of 1000 mL will develop severe anaemia (Hb < 8 g/dL), which can be associated with lethargy, decreased mental alertness, physical weakness, poor concentration and a predisposition to post-natal depression [2–4].

Red blood cell (RBC) transfusions have traditionally been used to manage severe anaemia in the pueperium however in the absence of clear transfusion triggers many women without severe symptoms will also receive blood transfusions. This places them at an increased risk of septicaemia, haematological reactions, delayed wound healing and thromboembolism, particularly if they receive multiple transfusions [5]. Blood products are also a scarce and costly resource [5]. Recent institutional guidelines and trial data suggest blood transfusions are likely to be appropriate in patients with Hb < 7 g/dL but not necessarily if alternative therapy is available or if the individual is clinically well compensated [5, 6].

Intravenous (IV) iron therapy has been shown to reduce the requirement for allogenic blood transfusion and can restore haemoglobin levels by an average of 2.5 g/dL at day 5 post infusion with peak effects observed at 3-6 weeks [2, 7–13]. Compared to RBC transfusions, newer iron preparations excluding dextran derivatives are cheap, display a more benign side effect profile than blood transfusions (<0.5% risk of serious adverse events, 1-3% risk of mild adverse events) and have single dosing regimens [14–16].

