### Major exclusion criteria

Age < 16 or >50 yearsRefuse consent to blood transfusion or iron infusionCo-morbidities necessitating rapid Hb restoration including: cardiac failure, ischemic heart disease, chronic renal failureKnown hematological malignancyKnown hemaglobinopathies requiring regular transfusionsSepsis (clinical or laboratory evidence—intrapartum fever >38.5 degrees with abnormal vital signs, positive blood culture)Contraindications to iron polymaltose (i.e. asthma, known hypersensitivity to iron polymaltose, chronic polyarthritis, acute renal dysfunction, uncontrolled hyperparathyroidism, infectious hepatitis and iron overload (ferritin >1000 ng/L)Severe symptoms of anemia including dyspnoea at rest, angina pectoris, syncope or transient ischemic attacks.

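### The per-arm suspension count and the unscheduled-meeting rule cover only anaphylaxis and haematological reaction; other serious harms depend on an undefined between-arm limb or the next scheduled meeting

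*Protocol article*

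**What the plan says.** All the rules stand in the protocol article under Monitoring/reporting of data.

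- **Suspension, first limb (within an arm):** "If the total incidence of severe adverse reactions (i.e. anaphylaxis, hematological reaction) exceeds 2 per 50 participants at any time in either treatment group".
- **Suspension, second limb (between arms):** "or if the difference in incidence of serious adverse events is greater than 50%, the study will be suspended until further review".
- **Unscheduled meetings:** "Unscheduled DSMB meetings will be called whenever severe adverse reactions occur in either treatment group".
- **Scheduled meetings:** a charter binds the members, "requiring them to convene every 2 months for the duration of the study".
- **Remit at those meetings:** the board is to "review the data for completeness, accuracy and to identify incidences and severity of any adverse reactions and their management".

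Two other sections name harms that bear on these rules. Background says of transfusion in women without severe symptoms: "This places them at an increased risk of septicaemia, haematological reactions, delayed wound healing and thromboembolism, particularly if they receive multiple transfusions". Major exclusion criteria lists the clinical picture of badly tolerated anaemia: "Severe symptoms of anemia including dyspnoea at rest, angina pectoris, syncope or transient ischemic attacks".

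**The concern.** The first limb and the unscheduled-meeting rule share the term *severe adverse reactions*, which the text closes with *i.e.* to two items. Both are reactions to a product that has been given. The harm most particular to the iron strategy is different: haemoglobin stays low for longer.

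The article itself describes that contrast. Women enter with Hb of 5.5 to 8.0 g/dL (Participants/eligibility criteria). Iron is said to raise Hb by 2.5 g/dL on average at day 5, with its peak at 3 to 6 weeks (Background). The transfused arm has Hb checked after each unit until it reaches at least 9.0 g/dL (Interventions). Table 1 schedules no further Hb between enrolment and Day 7.

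The primary objective includes showing that adverse outcomes do not become more frequent, and the monitoring section justifies the board by the possibility of serious adverse events with either treatment. The event definition that drives two of the three reactive rules is narrower than both statements. At stake is how promptly the board sees a serious event that is not a product reaction.

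**Working it through.** The article gives no operating characteristics for its rules, so there is no figure to reproduce. The check has three parts.

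**1. Which event meets which rule, on the text**

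| Event | Named in | Per-arm count | Unscheduled meeting | Between-arm limb |
|---|---|---|---|---|
| Anaphylaxis | Monitoring/reporting of data | yes | yes | if serious |
| Haematological reaction | Monitoring/reporting of data; Background | yes | yes | if serious |
| The four severe signs of anaemia, when due to anaemia | Major exclusion criteria | no | no | if serious |
| Septicaemia, thromboembolism, delayed wound healing | Background | no | no | if serious |

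All four severe-anaemia signs, and three of the four transfusion harms named in Background, fall outside the two rules built on *severe adverse reactions*. Their only reactive route is the between-arm limb.

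**2. How far the between-arm limb can be relied on**

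Let a and b be the numbers of women with a serious adverse event among n per arm, independent binomials. The event rates are assumptions, because the article gives none for this setting. Each probability is for a single look.

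- *Absolute reading:* fires if |a − b|/n > 0.5. With n = 50 this needs a difference of at least 26 women. Ten events against none is 10/50 − 0/50 = 20 percentage points, so no suspension.
- *Relative reading:* fires if the larger count exceeds 1.5 times the smaller, so one event against none fires.

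Exact enumeration over all (a, b):

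| n per arm | Assumed rates | Absolute | Relative |
|---|---|---|---|
| 50 | 2% and 2% | below 0.0001 | 0.67 |
| 50 | 2% and 10% | below 0.0001 | 0.91 |
| 50 | 5% and 30% | 0.0002 | 0.997 |
| 116 | 2% and 2% | below 0.0001 | 0.63 |
| 116 | 5% and 30% | below 0.0001 | 1.00 |

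On the absolute reading the limb is practically inert. On the relative reading it fires more often than not at equal 2% rates, so a signal says little.

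On either reading it cannot see a harm raised equally in both arms. Five serious events of 50 in each arm give a difference of 0, although 5/50 = 10% is above the 2/50 = 4% that governs reactions.

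**3. What a wider event list would do to the per-arm limit**

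Exceeding 2 per 50 means 3 or more of 50. For a true rate p, the probability is 1 − Σ C(50, k) p^k (1 − p)^(50 − k), summed over k = 0, 1, 2:

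| True rate p | Probability of 3 or more of 50 |
|---|---|
| 0.5% | 0.002 |
| 1% | 0.014 |
| 2% | 0.078 |
| 4% | 0.32 |
| 10% | 0.89 |

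The rule applies at any time, so repeated looks would add to these single-look figures. Moving more events into this count while leaving the limit alone would therefore change how often the trial is suspended.

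**The case against.** A reader might infer that harms other than acute reactions can never suspend the trial or reach the board. The documents do not support that. The same sentence goes on to a second limb that is not confined to reactions, and angina, septicaemia or thromboembolism recorded as a serious adverse event would count there. The board also meets every two months whatever has happened. Nor is the narrow term strictly confined to acute events, since a haematological reaction need not be acute. For the same reason it would be wrong to call the monitoring one-sided: a between-arm comparison of serious events is the kind of rule that can show an excess in the iron arm.

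Three further points deserve weight.

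- The bracket may have been meant as illustration. Interventions lists dyspnoea, syncope and circulatory collapse among the effects watched for during the infusion. But that covers them as infusion effects, and *i.e.* on its face closes the list.
- The board's charter and the full protocol are not shown and may hold event definitions or expedited reporting. If so, they differ from the published rule, and the published text still needs reconciling.
- The harms are collected: Follow up provides a checklist examination for infection and other adverse outcomes at Days 7, 14 and 28. Collection is not the same as a trigger, however.

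The objection to widening the suspension count without revisiting its limit stands in full, and the fix respects it.

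**Conclusion.** The point holds in a limited form. Two of the three reactive rules, and the wording of the two-monthly safety remit, rest on reactions, while the remaining suspension limb rests on serious adverse events. A serious complication of uncorrected anaemia, or septicaemia or thromboembolism in either arm, is left to a between-arm comparison whose scale is not stated, or to the next scheduled meeting. One such event can wait up to two months where a single anaphylaxis would call a meeting.

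This rests on reading *i.e.* as defining, and on there being no expedited reporting in the unseen charter. The probabilities rest on assumed event rates, but the contrast between the two readings of 50% does not turn on any one of them. This is a gap in safety oversight that should be closed; it does not affect the primary efficacy analysis.

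**What to change.** In Monitoring/reporting of data, and in the charter to match:

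1. Reconcile the two terms. Use one defined term, serious adverse events in either arm from randomisation to Day 28, for both the unscheduled-meeting rule and the board's review remit. State that it includes the events already named in Background and Major exclusion criteria when they are serious.
2. State whether the 50% difference is absolute or relative.
3. If the same term is also adopted for the per-arm suspension count, the sponsor and the board should re-examine the 2-per-50 limit at the same time, because a wider list would make it fire more often. Which events should suspend the trial, and at what number, is for them to settle.

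The cost is about one paragraph in the protocol and the charter, and some additional unscheduled meetings. The scheduled visits already assess infection and other adverse outcomes.

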## Discussion

Moderate to severe acute post-partum anaemia is associated with a number of short and long-term adverse health outcomes hence active treatment is necessary and is commonly indicated by a combination of haemoglobin and iron deficit and symptom severity. Whilst RBC transfusion is the mainstay treatment for severe symptomatic anaemia, wide practice variations exist in the management of mild-moderate anaemia in otherwise clinically stable women. If over treated with blood products, these women are placed at risk of transfusion related adverse effects, which although uncommon, can be life threatening and are almost always associated with ongoing morbidity.

The argument supporting expectant management for these patients has been well outlined in recent studies though there is no standard definition of what expectant management entails. Some institutes advocate the use of oral iron only whilst others prescribe parenteral replacement. Long term data indicates that parenteral iron is faster and more effective than oral iron at restoring haemoglobin and total body iron deficits and has the added advantage of avoiding gastrointestinal side effects which often interrupt compliance in the post-natal cohort [2, 3, 24]. Moreover, the lag period to replenish iron stores and induce erythropoeisis is significantly contracted with IV compared to oral therapy. This, coupled with an attractive safety and tolerance profile as well as being cheaper and more available, introduces parenteral iron as an appropriate alternative to blood transfusions in selected women.

If our study hypotheses are true then intravenous iron presents as a safer, sustained and more cost-effective alternative to blood transfusion in the management of hemodynamically stable women with acute post-partum anaemia. Our findings will be particularly useful for patients ineligible for treatment with blood products due to clinical or religious reasons and in under-resourced settings both within Australia and internationally. Ultimately we would hope these findings support the widespread implementation of parenteral iron into routine post-natal practice policies in an effort to improve patient safety and minimise resource wastage.

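### The between-arm safety trigger of a difference above 50% has no scale and no minimum count, and neither reading of it gives a usable suspension rule

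*Protocol article*

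**What the plan says.** The rule is in the protocol article under Monitoring/reporting of data. It has two limbs, and meeting either one suspends the study.

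- **Per-arm limb.** It opens "If the total incidence of severe adverse reactions (i.e. anaphylaxis, hematological reaction" and is met when that incidence "exceeds 2 per 50 participants at any time in either treatment group".
- **Between-arm limb.** The sentence continues "or if the difference in incidence of serious adverse events is greater than 50%, the study will be suspended until further review".

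The same section sets the surrounding oversight. The board's charter has members "requiring them to convene every 2 months for the duration of the study". In addition, "Unscheduled DSMB meetings will be called whenever severe adverse reactions occur in either treatment group". Ending the trial is a separate step: "Final decisions to terminate the study will be made by study researchers in consultation with the DMSB and the ethics committee".

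On expected rates, the Background gives newer intravenous iron preparations a "<0.5% risk of serious adverse events, 1-3% risk of mild adverse events". No rate is given for transfusion; the Discussion says only of its adverse effects "which although uncommon, can be life threatening".

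**The concern.** The between-arm limb is a numeric rule with an automatic consequence, but a difference in incidence above 50% can mean two very different things. It may mean more than 50 percentage points, or one incidence more than 50% higher than the other. For rare events these readings lead to opposite actions on the same data. With one event in one arm and none in the other, the relative reading suspends the trial. With a large real excess in one arm, the absolute reading does not. No minimum number of events or women limits either reading.

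The per-arm limb has a related gap. Two per 50 at any time can be a count within 50 women or a running proportion above 4%, and these behave differently early in recruitment.

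The limbs also count different things: severe adverse reactions in one, serious adverse events in the other. Severity is not seriousness, and a reaction implies attribution to treatment where an event does not.

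This is the only between-arm trigger the article states, in a trial whose primary objective includes showing no increase in adverse outcomes. At stake is whether it would react to a real excess, and how often it would pause recruitment when there is none.

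**Working it through.** The article states no chance of suspension, so there is no figure to reproduce. The check works out how each reading would behave.

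**Inputs**
- 250 women in total (Statistics) allocated 1:1 (Procedures, recruitment and randomisation), so about 125 per arm.
- Serious event risk with intravenous iron: below 0.5% (Background). This is an upper bound for one arm only.
- Risk with transfusion: not given. Equal risks of 0.1%, 0.5% and 1% in both arms are assumed, to show a range.
- Arms are assumed to fill in pairs, with the rule checked after each pair.

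**Between-arm limb, absolute points**
- At full enrolment, half of 125 is 62.5, so 63 events against 0 are needed.
- In the first pair, 1/1 against 0/1 is 100 points and meets it. In the second, 1/2 against 0/2 is exactly 50 points and does not exceed it. With equal 0.5% risks, one event in the first pair has probability 2 × 0.005 × 0.995 = 0.00995. That accounts for essentially the whole 1% chance of firing.
- From 10 women per arm to the end, exact recursion over both arms' event counts gives:

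| True risks | Chance of ever exceeding 50 points |
|---|---|
| 0.5% v 5% | below 0.0001 |
| 0.5% v 10% | 0.0003 |
| 0.5% v 20% | 0.014 |

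A 40-fold excess (20/0.5) would therefore almost never be caught.

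**Between-arm limb, relative**
- One event against none is more than 50% higher, so the first event meets it. The chance of firing is close to the chance of any event among 250 women, 1 − (1 − p)^250:
  - p = 0.1%: 1 − 0.999^250 = 0.221
  - p = 0.5%: 1 − 0.995^250 = 0.714
  - p = 1%: 1 − 0.99^250 = 0.919
- The exact recursion, which allows for both arms having an event in the same pair, gives 22%, 71% and 92%.
- Starting the comparison only at 50 per arm hardly helps: 70% at 0.5% and 89% at 1%.

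**Per-arm limb, running proportion above 4%**
- 1/24 = 4.2% exceeds 4%; 1/25 = 4.0% does not. One event is enough up to 24 women, two are needed from 25, and three from 50.
- At 0.5% risk, 1 − 0.995^24 = 0.113 is the chance of an event in the first 24. The exact chance of ever crossing over 125 women is 12.1% per arm, or 1 − (1 − 0.121)² = 22.7% in at least one arm. At 0.1% it is 2.4% per arm.

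**Per-arm limb, three or more events in the first 50**
- Binomial tail P(X ≥ 3), n = 50: 0.2% at 0.5% risk, 1.4% at 1%, 77% at 8%. One event cannot meet it.

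At 0.5% risk, the two readings of the per-arm limb differ about 60-fold in the chance of firing (12.1% against 0.2%).

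**The case against.** A reader might infer that the whole suspension rule cannot tell harm from chance, or that one early event is bound to suspend the trial. The text does not support either. The per-arm limb names a count and a denominator, and as a count it separates a 0.5% risk from an 8% risk well. The phrase at any time permits the running-proportion reading but does not require it.

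A reader might also infer that participants lack protection without the 50% limb, or that a chance trigger ends the trial. Neither follows. The board includes a statistician, meets every two months, and meets again after any severe reaction. The rule brings suspension pending review, and termination is decided separately. For severe reactions, the relative reading adds only a pause to a meeting that would be held anyway. A pause rule that leans towards sensitivity can also be a deliberate choice. That meeting is tied to severe reactions, however, so it does not necessarily cover the serious events that the between-arm limb compares.

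It cannot be claimed that the board would have to pick a reading after seeing data by arm. Members receive a charter before the study starts, it is not shown, and it may settle the scale. The article's own sentence would still need correcting: it states a rule, and no choice of scale alone makes that rule work.

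Finally, the 0.5% figure is an upper bound, for iron only, and for serious events. Applying it to transfusion or to severe reactions is an assumption, and at lower rates the false-trigger figures fall.

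**Conclusion.** The point stands for the between-arm limb on either scale. In absolute points it is practically unreachable after the first few women (0.014 from 10 per arm even at 0.5% against 20%). In relative terms it fires on the first event, in 22%, 71% and 92% of trials at equal risks of 0.1%, 0.5% and 1%. This is a defect in a stated rule, not detail left to another document.

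For the per-arm limb the finding is narrower: its denominator needs fixing. Only the running-proportion reading lets a single early event suspend the trial. The two event terms must also be reconciled.

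The absolute-scale conclusion hardly depends on the assumed rates. The relative-scale percentages do, and they rest on equal risks, about 125 women per arm and a check after each pair. The practical cost of a false trigger is a temporary suspension, so the rule should be corrected but does not undermine the trial.

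**What to change.** In Monitoring/reporting of data and in the board's charter:

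1. Replace the 50% difference with a between-arm rule on a stated scale, written as event counts by number treated, with a minimum number of events or participants before it applies.
2. State whether 2 per 50 is a count or a running proportion, and the minimum denominator from which it applies.
3. Use one defined type of event in both limbs, or define each and say why they differ.
4. Report the chance of suspension under the rule with and without excess harm, over a range of assumed rates that includes a stated assumption for transfusion.

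The thresholds are for the board and the sponsor to set; none is proposed here.

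The cost is one protocol paragraph and a charter revision. The downside is that a single early event would no longer suspend the study automatically, as it does on some present readings. The unscheduled meeting already required after each severe reaction covers most of that loss.
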